**Secondary outcomes**			
Fear	Subscale of the German 17-item version of the CAQ [16]	Continuously, 0 to 4 points	T0, T1, T2, T3
Avoidance	Subscale of the German 17-item version of the CAQ [16]	Continuously, 0 to 4 points	T0, T1, T2, T3
Attention	Subscale of the German 17-item version of the CAQ [16]	Continuously, 0 to 4 points	T0, T1, T2, T3
Change in score for cardiac anxiety	Total score of the German 17-item version of the CAQ [16]	Continuously, − 4 to 4 points	T1, T2, T3
Decrease in cardiac anxiety by 0.2 points	Total score of the German 17-item version of the CAQ [16]	Binary, yes/no	T1, T2, T3
Depression	PHQ-D [25]	Continuously, 0 to 27 points	T0, T1, T2, T3
Generalized anxiety	PHQ-D [25]	Continuously, 0 to 21 points	T0, T1, T2, T3
Somatization	PHQ-D [25]	Continuously, 0 to 30 points	T0, T1, T2, T3
Functional capacity	IRES-24 [26]	Continuously, 0 to 10 points	T0, T1, T2, T3
Blood pressure	Clinical examination	Continuously, systolic/diastolic in mmHg	T0, T1
Endurance	Clinical examination	Continuously, ergometer performance in watts/kg	T0, T1
General health	Visual analog scale of the EQ-5D [27]	Continuously, 0 to 100 points	T0, T1, T2, T3
Health-related quality of life	EQ-5D [28]	Continuously, health state of 11111 corresponds to a value of 1	T0, T1, T2, T3
Motivation to change lifestyle	OutCaRe [31]	Binary, certainly or rather yes vs. uncertain or less	T0, T1
Weekly physical activity	BSA-F [33]	Continuously, minutes	T0, T1, T2, T3
Self-efficacy to exercise	ESES [32]	Continuously, 10 to 40 points	T0, T1, T2, T3
Smoking status	Own development	Binary, yes/no	T0, T1, T2, T3
Weight	Clinical examination	Continuously, body mass index in kg/m²	T0, T1, T2, T3
Self-rated work ability	Work Ability Score [34]	Continuously, 0 to 10 points	T0, T1, T2, T3
Sickness absence	Own development	Binary, yes/no	T0, T2, T3
Sickness absence duration	Own development	Continuously, cumulative sickness absence in the last 3 or 12 months in weeks	T0, T2, T3
Stable return to work	[36]	Binary, yes/no	T2, T3
Time to stable return to work	[36]	Continuously, weeks	T2, T3
Employment	Own development	Binary, yes/no	T0, T2, T3
Disability pension	Own development	Binary, yes/no	T0, T2, T3
Capacity for last job	Medical assessment, standardized medical discharge report [37]	Binary, at least six hours per day or less than six hours per day	T1
Capacity for other job	Medical assessment, standardized medical discharge report [37]	Binary, at least six hours per day or less than six hours per day	T1

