Treatments during the rehabilitation program	Standardized medical discharge report [37], coding according to the classification of therapeutic services report [39]	Continuously, minutes or hours	T1
Content of the cognitive-behavioral rehabilitation program	[14]	Continuously, 0 to 12 points	T1
Consistency of the approach	[14]	Continuously, 0 to 16 points	T1
Gain in competence	[14]	Continuously, 0 to 40 points	T1
Recommendations for subsequent services	Standardized medical discharge report [37]	Binary, yes/no for 12 subsequent services	T1
Utilization of medical and non-medical services	FIMA [40]	Continuously, resource usage in euro	T3
Diagnoses	Standardized medical discharge report [37], clinical interview[42]	Nominal	T1
Sociodemographic data	Own development	Various (native language, number of children, level of school education, vocational qualification)	T0

*BSA-F* Physical Activity, Exercise, and Sport Questionnaire (German: Bewegungs- und Sportaktivität Fragebogen), *CAQ* Cardiac Anxiety Questionnaire, *ESES* Exercise Self-Efficacy Scale, *EQ-5D* European Quality of Life 5 Dimensions, *FIMA* Questionnaire for Health-Related Resource Use in an Elderly Population (German: Fragebogen zur Erhebung von Gesundheitsleistungen im Alter), *IRES-24* Indicators of rehabilitation status (German: Indikatoren des Reha-Status), *OutCaRe* Outcome of Cardiac Rehabilitation, *PHQ-D* Patient Health Questionnaire, *T0* Beginning of the rehabilitation, *T1* End of the rehabilitation, *T2* 3-month follow-up, *T3* 12-month follow-up

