### Sample size

As a minimum important difference for the 12-month follow-up, we defined 0.2 points of the total cardiac anxiety score (0 to 4 points [15, 16]). Although 0.2 points represent only 5% of the scale range, we consider this small gain to be relevant because we are comparing two comprehensive rehabilitation programs. Assuming a standard deviation of 0.6 points [43], 0.2 points correspond to a standardized mean difference of 0.33. To detect this difference with a two-sided error of 5% and a power of 80%, 286 participants are required. Further assuming a response rate of 70% in the 12-month follow-up, we plan to recruit 410 participants (intervention group: n = 205; control group: n = 205) to be able to detect the minimal important difference also in a complete-case analysis. For our primary intention-to-treat analysis with multiple imputation of missing follow-up scores, a difference of 0.2 points is detected with a power of about 92%.

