### Statistical methods

We will analyze short-term (end of rehabilitation and 3-month follow-up) and long-term effects (12-month follow-up) using different models and publish the findings separately. We will use mixed models if more than one measurement point needs to be considered, i.e., end of rehabilitation and 3-month follow-up, and generalized linear models otherwise. If baseline scores are available, these will be included as a covariate when estimating the treatment effect. If outcomes are binary, a logit link will be used. High depression, high generalized anxiety, and high cardiac anxiety, as well as age, sex, and education, are tested as possible moderators of the treatment effect on our primary outcome cardiac anxiety assessed at the 12-month follow-up.

For health economic evaluation, we will calculate an incremental cost-effectiveness ratio [44]. Assessments of costs employ a societal perspective [41, 45]. Effectiveness is measured using quality-adjusted life years as derived from the 12-month assessment of the EQ-5D-5 L [28, 30]. The incremental cost-effectiveness ratio is calculated by dividing the difference in costs between both interventions by the difference in effectiveness between both interventions. Bootstrapping is used to compute a 95% confidence interval of the incremental cost-effectiveness [44].

Missing data will be imputed using chained equations [46]. We will create 20 independent data sets with complete values. Parameter estimates of the models will be combined in accordance with Rubin’s rules [47]. Statistical tests will be regarded as significant if the two-sided p-value of a test is less than 0.05. An up-to-date version of Stata (StataCorp, College Station, Texas, USA) will be used to conduct the analyses.

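### The ICER's effectiveness difference has no stated adjustment for the baseline EQ-5D-5L index, although that index is collected and the plan's other models adjust for baseline

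*Protocol article*

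**What the plan says.** The economic paragraph of the Protocol article, Statistical methods, sets out three things.

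- The effectiveness measure: "Effectiveness is measured using quality-adjusted life years as derived from the 12-month assessment of the EQ-5D-5 L".
- The ratio: "The incremental cost-effectiveness ratio is calculated by dividing the difference in costs between both interventions by the difference in effectiveness between both interventions".
- The uncertainty: "Bootstrapping is used to compute a 95% confidence interval of the incremental cost-effectiveness".

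No regression model and no covariate appear there.

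The paragraph before it, on the mixed and generalized linear models, has a general rule: "If baseline scores are available, these will be included as a covariate when estimating the treatment effect".

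Table 2 lists the EQ-5D index as a secondary outcome at all four measurement points: "Continuously, health state of 11111 corresponds to a value of 1 T0, T1, T2, T3". A T0 value is therefore planned for both arms. The resource-use questionnaire is listed at the 12-month follow-up only ("Continuously, resource usage in euro T3"), so it gives no baseline cost to adjust for. The point concerns the denominator of the ratio.

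**The concern.** A patient's utility a year after rehabilitation is usually related to utility at the start. If the two arms differ at T0 by chance, part of that difference reappears in an unadjusted 12-month comparison. The T0 index would remove that part and narrow the interval, and it is already being collected.

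This matters more in a ratio than in an ordinary mean difference. The QALY difference is the divisor. The Sample size section itself expects only a small gain on the primary outcome, because two comprehensive programs are compared. If the utility gain is small too, a shift of one or two hundredths can change the ratio greatly or reverse its sign. The Discussion says the results are to inform pension insurers on wider implementation.

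There is also a question of consistency. The baseline rule plainly covers the EQ-5D index as a secondary outcome. The trial could therefore report a baseline-adjusted 12-month EQ-5D effect and an ICER built on a differently estimated effect from the same instrument and visit.

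**Working it through.** **The plan's own figures, which fix the patient numbers.** The protocol states no utility SD, QALY difference or ICER precision. Its primary-outcome calculation gives the arm sizes and reproduces. With a difference of 0.2, an SD of 0.6, two-sided 5% and 80% power, the t-test needs 142.2 per arm, so 143 per arm or 286 in total. Dividing by the 70% response rate gives 286 / 0.70 = 408.6, planned as 410 or 205 per arm. Power with 205 per arm is 0.92, as stated. The complete-case size is thus 143 per arm and the imputed analysis uses 205. Imputation does not recover all the lost information, so the effective size lies between the two.

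**Assumptions not in the documents.**
- Utility SD 0.15 to 0.25.
- Correlation ρ between the T0 and 12-month index 0.4 to 0.7.
- The 12-month utility difference is read as the QALY difference over one year, since the article does not describe the conversion.

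**Formulas.**
- SE of an unadjusted difference, and of the T0 difference at the same SD: SD × √(2/n).
- SE with the T0 index as covariate: SD × √(2/n) × √(1 − ρ²).
- Shift of the unadjusted difference for a one-SE imbalance at T0: ρ × SD × √(2/n).

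√(2/205) = 0.0988 and √(2/143) = 0.1183.

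| n per arm | SD | Unadjusted SE (= one-SE T0 imbalance) | Shift, ρ 0.4 to 0.7 | Adjusted SE, ρ 0.4 to 0.7 |
|---|---|---|---|---|
| 205 | 0.15 | 0.0148 | 0.0059 to 0.0104 | 0.0136 to 0.0106 |
| 205 | 0.20 | 0.0198 | 0.0079 to 0.0138 | 0.0181 to 0.0141 |
| 205 | 0.25 | 0.0247 | 0.0099 to 0.0173 | 0.0226 to 0.0176 |
| 143 | 0.15 | 0.0177 | 0.0071 to 0.0124 | 0.0163 to 0.0127 |
| 143 | 0.20 | 0.0237 | 0.0095 to 0.0166 | 0.0217 to 0.0169 |
| 143 | 0.25 | 0.0296 | 0.0118 to 0.0207 | 0.0271 to 0.0211 |

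**Relative gain, whatever the SD and n.** At ρ = 0.4, √(1 − 0.16) = 0.917, a cut of 8%. At ρ = 0.7, √(1 − 0.49) = 0.714, a cut of 29%. In patient numbers this is worth 1/0.84 = 1.2 to 1/0.51 = 2.0 times as many. At a weaker correlation of 0.3, √(1 − 0.09) = 0.954 and the cut is only about 5%.

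**Does the general rule already settle it?** It speaks of baseline scores of outcomes analysed by the named models. A QALY has no baseline score of its own; the covariate needed is the T0 utility index, which the economic paragraph does not mention. That paragraph names two differences and a bootstrap, and no model. An analyst could follow the text faithfully and either adjust or not.

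**The case against.** The strongest reply is that dividing a cost difference by an effectiveness difference defines any ICER, adjusted or not. A reader might infer that the plan has chosen raw differences and decided to ignore baseline utility. The documents do not support that: neither is written, and the baseline rule in the same section carries no exception. Reading it as covering the effectiveness difference is reasonable. What remains is that the rule's reach is unclear.

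A reader might also infer bias. Under one-to-one randomisation there is none. Chance imbalance at T0 is ordinary sampling variation, and a bootstrap interval for the unadjusted estimate reflects it. The loss is in precision, together with a shift conditional on the imbalance actually observed.

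A larger gain could be claimed by building QALYs from all four visits, which would tie them more closely to T0. The protocol derives effectiveness from the 12-month assessment, so that gain is not used here.

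Finally, this is a condensed article, and the estimator for incremental QALYs is often left to an analysis plan, which may settle it. That lowers the weight of the point. It does not remove it, because the article states its own formula for the ratio and the data analysis is not blinded, so the choice is better fixed beforehand.

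**Conclusion.** The point holds as a free improvement to a secondary analysis. The economic paragraph specifies no adjustment for a baseline utility that is collected, and the neighbouring rule does not clearly reach it. Taken literally, the text gives an unbiased QALY difference that is less precise than it need be, moves with any chance T0 imbalance, and may not match the adjusted 12-month EQ-5D effect.

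The size is a shift of about 0.006 to 0.021 for a one-standard-error T0 imbalance of about 0.015 to 0.030, and a standard error that adjustment would cut by about 8 to 29%. These figures rest on the assumed SD and correlation. Only the patient numbers come from the protocol. The primary outcome and its sample size are untouched.

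**What to change.** Add one sentence to the health economic analysis: the incremental QALY used in the ICER is the arm coefficient from a regression of each patient's QALY on arm and T0 EQ-5D-5L index, refitted in every bootstrap replicate and every imputed data set, with the unadjusted difference reported alongside. If adjustment was always intended, the sentence simply makes that explicit.

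The cost is one sentence and one extra covariate in the bootstrap code. No new data and no additional patients are needed.

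### The bootstrap 95% confidence interval planned for the cost-effectiveness ratio cannot be interpreted if the QALY difference is not clearly separated from zero; net monetary benefit over prespecified thresholds would avoid this

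*Protocol article*

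**What the plan says.** The economic plan is one paragraph of the protocol article, under Statistical methods. Costs are taken from society's viewpoint ("Assessments of costs employ a societal perspective"). On the effect side, "Effectiveness is measured using quality-adjusted life years as derived from the 12-month assessment of the EQ-5D-5 L". The summary measure is obtained by "dividing the difference in costs between both interventions by the difference in effectiveness between both interventions". Its uncertainty is handled in one sentence: "Bootstrapping is used to compute a 95% confidence interval of the incremental cost-effectiveness". A methods source is cited there. The text does not name the type of bootstrap interval, a willingness-to-pay threshold, or the treatment of replicates whose QALY difference is zero or negative.

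No expected QALY difference, QALY SD, cost difference or cost SD appears anywhere. The effect-size figures under Sample size concern cardiac anxiety only: "Assuming a standard deviation of 0.6 points [43], 0.2 points correspond to a standardized mean difference of 0.33". There the sponsor explains the modest target: "we consider this small gain to be relevant because we are comparing two comprehensive rehabilitation programs".

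**The concern.** A ratio can be ordered from favourable to unfavourable only while its denominator keeps one sign. A cost difference of -500 euros with a QALY difference of +0.02 gives -25,000. A cost difference of +500 with a QALY difference of -0.02 also gives -25,000. The first replicate says the new programme is cheaper and better, the second that it is dearer and worse. Positive ratios have the same ambiguity: dearer-and-better and cheaper-and-worse share a sign but call for opposite readings. Replicates with a denominator close to zero produce arbitrarily large values of either sign.

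The trial compares two full rehabilitation programmes and is sized on a disease-specific scale, so a QALY difference that is not clearly separated from zero is a realistic outcome. The Discussion commits to publishing whatever the size or direction of the effects, and says the results should inform pension insurers about wider implementation. The planned measure should therefore remain readable when the QALY difference is small, zero or negative.

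**Working it through.** **The plan's own figures.** These fix the numbers per arm used below. With a difference of 0.2 and SD 0.6, the normal formula gives 2 × (1.96 + 0.84)² × (0.6/0.2)² ≈ 141.3, so 142 per arm. The t-test version gives 284.5 in total, or 286 with equal arms (143 each). 286 / 0.70 = 408.6, rounded to 410 (205 each). Power with 205 per arm is 0.921. The stated 286, 410 and about 92% are all reproduced. For the economic analysis, 143 per arm stands for complete cases and 205 for full information on everyone randomised.

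**When a ratio has a bounded 95% set.** Let C and Q be the estimated cost and QALY differences, with standard errors s_C and s_Q, taken as normal and independent. The 95% set for the ratio R contains every R with (C − R·Q)² ≤ 1.96² × (s_C² + R²·s_Q²). The coefficient of R² is Q² − 1.96²·s_Q². The set is bounded only if this is positive, that is, if |Q|/s_Q > 1.96. This is Fieller's condition, and it does not depend on the type of bootstrap interval. It fails exactly when the 95% interval of the QALY difference includes zero.

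**How often it fails.** For an assumed standardized QALY effect d and n per arm, put k = d·√(n/2). The chance that the interval includes zero is Φ(1.96 − k) − Φ(−1.96 − k). For example, d = 0.2 and n = 205 give k = 0.2 × 10.12 = 2.02 and a chance of 0.474.

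| Assumed d | 143 per arm | 205 per arm |
|---|---|---|
| 0 | 95.0% | 95.0% |
| 0.1 | 86.5% | 82.7% |
| 0.2 | 60.6% | 47.4% |
| 0.25 | 43.9% | 28.4% |
| 0.333 (anxiety effect carried over) | 19.5% | 7.9% |

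The chance that the point estimate itself is zero or negative is smaller: 19.9% / 15.6% at d = 0.1, 4.5% / 2.1% at 0.2, and 0.2% / under 0.1% at 0.333.

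**Illustration.** All inputs are assumed: 205 per arm, QALY SD 0.2, cost difference 500 euros, cost SD 8,000 euros, costs and QALYs independent, replicates centred on d = 0.1.
- QALY difference 0.1 × 0.2 = 0.02; ratio 500 / 0.02 = 25,000 euros per QALY.
- Percentile interval of the ratio: about −343,000 to +388,000.
- Replicates: 62.3% dearer and better, 22.1% cheaper and better, 11.4% dearer and worse, 4.1% cheaper and worse. The second and third groups together form the negative ratios.
- Net monetary benefit at an assumed 30,000 euros per QALY: 30,000 × 0.02 − 500 = 100 euros, with interval −1,832 to 2,032 from the same replicates.
- At thresholds of 0, 10,000 and 50,000 it is −500, −300 and +500 euros.

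**Coverage.** In simulated trials with the same assumed SDs and cost difference, d from 0.05 to 0.333 and both arm sizes, the percentile interval of the ratio covered the true value 96 to 99% of the time. The net monetary benefit interval covered 94 to 95%.

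**The case against.** The article does not say that the interval is a percentile interval. It cites a source for the method, and a fuller economic plan may exist that covers replicate handling, the cost-effectiveness plane and an acceptability curve. It would be wrong to count those as missing. That much stands. The point here is narrower: the article does fix a 95% interval for a ratio, and the boundedness condition applies whichever bootstrap interval is used.

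Four stronger readings are tempting and are not supported:
- A reader might infer that a QALY difference near zero is established as likely. The documents contain no QALY figure. The 0.2-point target is a minimum important difference on the anxiety score, not a forecast for utilities, and at d = 0.333 the problem is uncommon.
- A reader might infer that the interval would tend to miss the true value or look falsely precise. The simulation showed coverage above 95%, and the illustrated interval was very wide. The defect lies in what the interval means.
- A reader might infer that the economic question could not be answered at all. The cost and QALY differences remain available, and Table 2 lists the EQ-5D index as a secondary outcome at 12 months, so the utility difference is also analysed outside the ratio.
- A reader might infer that baseline utility goes unadjusted. Statistical methods includes baseline scores as covariates where available, and Table 2 has the EQ-5D at baseline.

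**Conclusion.** The concern holds in conditional form. The article rests economic uncertainty on a confidence interval for a ratio, and that interval cannot be interpreted once the QALY difference is not clearly separated from zero. This is more likely than not, or close to it, if the true QALY effect is about 0.2 SD or less (47% to 61% at 0.2, 83% to 86.5% at 0.1). It is a minority risk of 8% to 20% if the effect is as large as the one assumed for anxiety. These figures assume normal sampling distributions and between 143 and 205 informative participants per arm; the standardized QALY effects are assumptions, not document figures. The euro amounts are illustrative only. The matter is confined to the economic evaluation and has no bearing on the primary outcome or the sample size.

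**What to change.** Amend the economic paragraph as follows:
- Report the incremental cost-effectiveness ratio as a point estimate only, alongside the cost difference and the QALY difference, each with its 95% confidence interval.
- Base inference on incremental net monetary benefit (threshold × QALY difference − cost difference), with a bootstrap 95% confidence interval at each value in a prespecified range of willingness-to-pay thresholds.
- Show the cost-effectiveness plane and acceptability curve from the same replicates.

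This needs no new data and no further resampling. It does require the sponsor to choose and justify the threshold range in advance. That is a substantive decision, because the sign of the net benefit can depend on it: in the illustration it changed between 10,000 and 30,000 euros per QALY. Fixing the range before the 12-month data are seen prevents a later choice of threshold that favours one conclusion.

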## Abstract

**Background:**

Depression, generalized and cardiac anxiety, and posttraumatic stress disorder negatively affect disease severity, participation, and mortality in patients with cardiovascular disease. Psychological treatments within cardiac rehabilitation may improve the outcomes of these patients. We therefore developed a cognitive-behavioral rehabilitation program for patients with cardiovascular disease and mild or moderate mental illness or stress or exhaustion. In Germany, similar programs are well established in musculoskeletal rehabilitation and cancer rehabilitation. However, no randomized controlled trials have evaluated if such programs achieve better outcomes in patients with cardiovascular disease compared with standard cardiac rehabilitation.

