### Harms

Although adverse events causally related to cognitive-behavioral rehabilitation are not expected, we will assess disability pensions and premature termination of rehabilitation in both groups.

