### Data collection methods

Data are collected via questionnaires, clinical examinations, and the standardized rehabilitation discharge reports. Questionnaires are completed at four measurement points: at the beginning and end of rehabilitation, as well as 3 and 12 months after completion of rehabilitation. The assessments have already been tested during the implementation of the intervention [14] and are described in detail above (Table 2). The 3-month and 12-month follow-up questionnaires are sent from the rehabilitation center. Patients whose follow-up questionnaires have not been received after two weeks are reminded twice at two-week intervals, if necessary. We enclose the questionnaire again with each reminder. Clinical examinations are performed at the beginning and end of rehabilitation. Treatments administered during rehabilitation are documented by the rehabilitation center in the discharge reports at the end of rehabilitation.

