### Confidentiality

Participants are added to a password-protected study list (Microsoft Excel) with their name, address, and social security number upon consent to participate and are assigned an identification number. This list also documents the treatment group, consent, and the planned start of rehabilitation after randomization. This study list remains at the recruiting rehabilitation center. The rehabilitation center transmits a pseudonymized copy of this list exclusively with the pseudonym, treatment group, date of receipt of consent and planned start of rehabilitation electronically and encrypted to the University of Lübeck at the beginning of each week. The study list will be shredded by the rehabilitation center after all follow-up questionnaires have been sent out. As of that point, the data will be completely anonymized.

The rehabilitation center documents in another list (Microsoft Excel), in which participants are recognized only by their identification number (pseudonymized list), their date of birth, gender, the actual start of rehabilitation and the end of rehabilitation (if necessary, also the early termination of rehabilitation), selected clinical data collected in the rehabilitation center (systolic and diastolic blood pressure, ergometer performance in watts/kg, capacity for last job and other job, recommendations for subsequent services, diagnoses), and the therapeutic services performed during rehabilitation.

The participants’ questionnaires are provided with the identification number in the rehabilitation center and handed over to the study participants by a member of the research team for completion at the beginning and end of the rehabilitation. The participants deliver the questionnaires in an envelope at the reception of the rehabilitation center. Thereafter, these questionnaires are personally handed over to MB by DB every two weeks. The questionnaires of the follow-up assessments after 3 and 12 months, also tagged with the identification number, as well as the reminders, are sent from the rehabilitation center. A stamped return envelope addressed to the University of Lübeck is enclosed with this letter.

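### No step is planned to learn of deaths after discharge, so they would be imputed as non-response in the QALY and cost analysis and be missing from harm reporting

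*Protocol article*

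**What the plan says.** The Statistical methods section gives one rule for incomplete data: "Missing data will be imputed using chained equations [46". It adds: "We will create 20 independent data sets with complete values". The Sample size section makes this the main analysis: "For our primary intention-to-treat analysis with multiple imputation of missing follow-up scores". QALYs are to come from the 12-month EQ-5D-5L and feed an incremental cost-effectiveness ratio. No value is given for a patient who has died.

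On data capture, the Harms section says "we will assess disability pensions and premature termination of rehabilitation in both groups" and names nothing else. Table 2 has no vital-status row. After discharge, the Data collection methods section describes contact by post only: "Patients whose follow-up questionnaires have not been received after two weeks are reminded twice at two-week intervals, if necessary".

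The Confidentiality section lists the fields of both centre lists and limits the weekly transfer to pseudonym, treatment group, date of consent receipt and planned start of rehabilitation. Death is in none of these. The section then says: "The study list will be shredded by the rehabilitation center after all follow-up questionnaires have been sent out".

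The Abstract's background states that the targeted conditions "negatively affect disease severity, participation, and mortality in patients with cardiovascular disease".

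**The concern.** A post-discharge death and an ignored questionnaire leave the same trace: nothing comes back. If nobody records which is which, the imputation model cannot treat them differently. The deceased patient then receives a 12-month EQ-5D value typical of survivors, although death counts as 0 on the QALY scale, together with costs for time not lived. The resulting error favours the arm with more deaths.

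Deaths by arm would also go unreported, in a cardiac trial whose rationale cites mortality and whose experimental programme intensifies exercise. An analysis plan written later could define how deaths are handled, but it could not supply a field that was never collected once the identifiers are gone.

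**Working it through.** **1. The plan's own figures.** Inputs from Sample size: difference 0.2, SD 0.6, two-sided 5%, power 80%, 70% response, 205 per arm.
- Required N: the t-test gives 284.5, so 286 in equal arms is reproduced within rounding.
- Recruitment: 286 / 0.70 = 408.6, so 409, or 410 in equal arms.
- Power of the imputed analysis: 0.2 / (0.6 × √(2/205)) = 3.375; 3.375 − 1.96 = 1.415; power 92.1%. The stated figure of about 92% thus counts all 410 randomised patients as having a 12-month score.
- Expected non-response: 0.30 × 410 = 123.

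**2. How many deaths could be hidden.** The document gives no mortality figure. Assumed 12-month range, for patients aged 18–65 with NYHA class III or worse excluded:

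| Assumed mortality | Deaths in 410 | Share of 123 non-responses |
|---|---|---|
| 0.5% | 2.1 | 1.7% |
| 1% | 4.1 | 3.3% |
| 2% | 8.2 | 6.7% |

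**3. Effect on the QALY difference.** Assumed imputed living utility 0.8 (range 0.7–0.9); value after death 0.
- *12-month value alone*, the literal reading of Statistical methods: 0.8 / 205 = 0.0039 per excess death in one arm (0.0034–0.0044 over the range). A net imbalance of 2 gives 0.0078; of 4, 0.0156.
- *Area under the curve, deaths spread evenly over the year*: on average half a year is lost, so 0.5 × 0.8 / 205 = 0.0020 per excess death.
- *Area under the curve by trapezoids, with only the 12-month value wrong*: that value carries weight (9/12)/2 = 0.375, so 0.375 × 0.8 / 205 = 0.0015 per excess death.
- *Scale*: with an assumed utility SD of 0.2 and 205 fully observed per arm, SE = 0.2 × √(2/205) = 0.0198. Imbalances of 2 and 4 are then 0.40 and 0.79 SE on the 12-month value alone, and about half that or less under an area-under-curve QALY. With some 30% imputed the SE is larger and these ratios fall further.

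**4. Effect on the primary analysis.**
- Severe assumed case: 3% deaths in one arm, with imputed cardiac anxiety scores wrong by a full SD. That arm's mean moves 0.03 × 0.6 = 0.018 points, against the 0.2-point target.
- Counting survivors only, power falls from 92.1% to 92.0%, 91.9% and 91.6% at 0.5%, 1% and 2% mortality.

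**5. A formal mortality comparison.** With 205 per arm, power to detect a halving of risk is about 8% (1% vs 0.5%) and 17% (3% vs 1.5%). Only descriptive reporting is worth asking for.

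**The case against.** The strongest reply is that the article never says post-death values count as missing data. How deaths enter the imputation, and what utility death takes, are matters commonly left to an analysis plan, which is not shown. That is fair: a reader might infer that the authors intend to impute for the dead, and the text does not support this. What remains is that no described field would let any later plan tell the two cases apart.

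A reader might also infer that deaths are never ascertained and that a mortality comparison is impossible. Both go too far. A death during the four-week stay would be known to the centre and could appear as early termination, which is recorded and assessed in both arms. The centre also holds names, addresses and social security numbers and sends the mailings itself, so it could check vital status before the list is shredded. The step is not planned, but it is feasible.

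The shredding rule is milder than it first looks. Each reminder encloses the questionnaire again, so the list reasonably survives until the last 12-month reminder has gone out. What is lost is the time after that mailing, when replies and returned post would arrive.

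Finally, the size rests on assumed mortality, utility, SD and imbalance. With four deaths in total, all four falling in one arm has probability 2 × (1/2)⁴ = 12.5% under equal risk. This limits the weight of the point but does not remove it.

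**Conclusion.** The point holds in a limited form. As written, the protocol has no step to ascertain death after discharge, an imputation rule without exception, and a planned destruction of identifiers that closes off later checking. The consequences fall on the QALY/ICER analysis and on harm reporting.

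Under the stated assumptions (0.5–2% mortality, living utility 0.8), the error is about 0.004 in the mean QALY difference per excess death on the 12-month value alone, and about 0.002 or less under an area-under-curve QALY. Even an imbalance of four deaths stays below one standard error. Because this difference is the denominator of the cost-effectiveness ratio, it would matter most if the true difference is small; the document gives no expected value.

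A reader might infer that the primary result is compromised. It is not: the shift is about 0.018 cardiac anxiety points even in the severe case, power changes by less than one percentage point, and the sample-size figures reproduce. The change is worth making because it is cheap and cannot be made once the list is shredded.

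**What to change.** 1. Add vital status and date of death, where known, to the pseudonymized list and to the transfer to the university. Sources are returned mail, relatives' replies, or a check using identifiers already held.
2. Shred the study list only after the last 12-month reminder period has closed and vital status has been entered.
3. Report deaths by arm descriptively, alongside disability pensions and premature termination in Harms.
4. In Statistical methods, state that values after a known death are not imputed: utility and costs are 0 from the date of death, and only pre-death costs are imputed. The latter is needed because resource use is collected only at 12 months.
5. State how deaths are handled in the primary analysis. A survivor-only estimand is one option but need not be adopted; it conditions on a post-randomisation event and departs from the declared intention-to-treat analysis.

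Cost: one list field, some follow-up of unreturned questionnaires, a short delay in shredding and a few sentences of analysis text. The data-protection description must change, because the weekly transfer is currently restricted to four items. An ethics amendment may be needed while recruitment is ongoing, and the consent wording, which is not shown, should be checked. No extra patients or visits are required.
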